#### B2. SIGNIFICANCE AND BACKGROUND FOR THE STUDY

| In the United States, 16 million persons, or almost 9% of adults, had diabetes in 2002 (1). Worldwide, an estimated 171 million persons have diabetes, and an alarming increase to 366 million persons is expected for the year 2030 (2). Type 2 diabetes accounts for 90-95% of all diagnosed cases of diabetes. Diabetes is associated with high rates of morbidity and premature mortality. Obesity increases risk of type 2 diabetes, hypertension, arthritis, cardiovascular diseases, several types of cancer, and premature mortality (3).  While increased physical activity and restriction of energy intake can substantially reduce incidence of type 2 diabetes (4) insight into the role of other lifestyle factors may contribute to additional prevention strategies for type 2 diabetes. Habitual consumption of coffee may have substantial beneficial effects on glucose metabolism according to recent findings of epidemiological studies in the U.S., Europe, and Japan (5). Coffee is among the most widely consumed beverages in the world. Knowledge on both the positive and negative health effects of coffee is important to allow individuals to make informed choices regarding coffee consumption. In addition, data on the health effects of different types of coffee can be used in public health recommendations and may contribute to disease prevention.  Coffee in relation to glucose metabolism and energy balance: potential mechanisms  Coffee is a beverage that contains hundreds of components including substantial amounts of chlorogenic acid, caffeine, magnesium, potassium, niacin (vitamin B3), trigonelline (N-methylnicotinic acid), and lignans (6-9). The table shows a selection of coffee components and suggested mechanisms for effects of these components on glucose metabolism. Most data on effects of coffee components on glucose metabolism are based on animal and *in vitro* studies, and the relevance for the weight gain and the development of type 2 diabetes in humans is currently unclear. However, the results suggest that an effect of coffee consumption on body fatness and glucose metabolism is biologically plausible, and that the effects of coffee cannot be equated with those of caffeine.  *Caffeine:* caffeine intake was associated with an acute reduction of insulin sensitivity in short-term metabolic studies in humans (10,11) This effect reflects decreased glucose storage, probably due to increased epinephrine release (11) Acute effects of caffeine through increased epinephrine levels cannot be extrapolated to long-term effects of coffee consumption, because acute effects of coffee on epinephrine are weaker than expected from its caffeine content (22) and because effects of caffeine on epinephrine levels wane after continued intake (23) Based on animal studies and metabolic studies in humans, beneficial effects of caffeine on glucose metabolism through increased uncoupling protein expression and lipid oxidation have also been suggested (12). Recent findings from observational studies indicate that the inverse association between coffee consumption and risk of type 2 diabetes cannot be explained caffeine. Decaffeinated coffee consumption was also associated with a lower risk of type 2 diabetes and with markers of insulin sensitivity (24,25). These results indicate that components of coffee other than caffeine can affect glucose metabolism, but do not rule out an effect of caffeine on energy balance and glucose metabolism.In rats, caffeine injections reduced energy intake and weight gain, an effect that may have been mediated by increased levels of corticotrophin-releasing factors or sympathetic activation (16). In humans, energy intake was increased during 2 days of caffeine withdrawal (26). In addition, short-term intervention studies have consistently shown that intake of caffeine or caffeinated coffee stimulates thermogenesis and increases energy expenditure (13-15).  Epidemiological studies on coffee consumption and risk of type 2 diabetes  We have recently conducted a systematic review on epidemiological studies on coffee consumption and risk of type 2 diabetes (5). Nine cohort studies on coffee consumption and risk of type 2 diabetes included a total of 193,437 participants and 8394 incident cases of type 2 diabetes. The summary multivariate-adjusted relative risk of type 2 diabetes was 0.65 (95% CI 0.54-0.78) for the highest (≥6 or ≥7 cups per day) and 0.72 (95% CI 0.62-0.83) for the second highest (4-6 cups per day) category of coffee consumption compared with the lowest category of coffee consumption (0 or ≤2 cups per day). In a recent prospective U.S. study, that was not yet included in the meta-analysis, coffee consumption was also inversely associated with risk of type 2 diabetes (27). In cross-sectional studies, coffee consumption was consistently associated with a lower prevalence of impaired glucose tolerance and type 2 diabetes (5). In several, but not all studies, higher habitual coffee consumption was associated with higher insulin sensitivity (5,28). Results from studies that included an oral glucose tolerance test suggested that coffee consumption affected postprandial glucose metabolism, rather than fasting glucose concentrations (5,29). Coffee consumption tends to be associated with lifestyle habits that increase risk of type 2 diabetes (e.g. cigarette smoking, lower physical activity) and more complete adjustment for confounding generally strengthened the observed inverse association between coffee consumption and risk of type 2 diabetes (5). Still, confirmation of the observed inverse association between coffee consumption and risk of type 2 diabetes in randomized trials of coffee consumption with appropriate outcome measures is desirable to completely rule out residual confounding as a potential explanation.    Previous intervention studies  Data from intervention studies on the effect of coffee consumption for longer than 1 day on glucose homeostasis is sparse. In an older study, 14 days of higher decaffeinated coffee consumption was associated with a decrease in plasma glucose concentrations (30). However, this intervention study did not include a control group. In a randomized cross-over study, 4 weeks of very high coffee consumption did not affect fasting glucose concentrations and increased fasting insulin concentration (31). This increase may reflect reduced hepatic extraction of insulin or direct effects of caffeine on insulin secretion,(31) and requires further study. Several studies have tested effects of caffeine intake of glucose levels and observed no effects (5). No randomized intervention studies have examined the effects of coffee consumption for longer than 1 day on postprandial glucose levels. This is of particular importance because coffee consumption was associated with lower postload (during an oral glucose tolerance test), rather than lower fasting glucose concentrations (5).Few studies have examined the effect of caffeine intake on weight loss. Intake of caffeine capsules for 24 weeks did not induce weight loss in obese persons (32). However, in an other study overweight and moderately obese persons who were habitual caffeine consumers lost more weight during a dietary intervention than those that did not consume caffeine (33).  Study significance:  Epidemiological studies have consistently shown an association between higher coffee consumption and a lower risk of type 2 diabetes. Confirmation of these findings in randomized trials of coffee consumption is desirable, and no randomized intervention studies of coffee consumption and glucose tolerance lasting longer then 1 day has been conducted. We propose this pilot study to demonstrate the feasibility of such a trial. If successful, this study will form the basis for a definitive trial of coffee consumption, body fatness, and glucose tolerance. Given the extensive use of coffee and the rapidly increasing health burden of type 2 diabetes and other obesity related disorders, such a trial would have important public health implications.  Preliminary Data: We have not yet conducted a coffee consumption trial, but an Australian trial of caffeinated and decaffeinated coffee protocol similar to that in the current study appeared to be well tolerated by participants with satisfactory compliance (34). |

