#### B3. DESCRIPTION OF RESEARCH PROTOCOL

##### A. Study Design

| For this pilot trial we will use an 8-week randomized intervention study comparing the effects of caffeinated coffee (n=15), decaffeinated coffee (n=15), and no coffee (n=15) consumption (see figure).  the study medications. The 8-week intervention will be preceded by a 2-week run-in phase with no coffee consumption. At the initial visit, the 4 week visit, and the 8 week visit an oral glucose tolerance test (OGTT) will be conducted and measures of body fatness will be assessed. At the 6-week visit a nonfasting blood sample will be obtained to measure caffeine concentrations. Although we recognize the potential advantages of a cross-over study, the compliance to the interventions is uncertain and a cross-over design is particularly sensitive to decreases in compliance over time. The intervention will be blinded to the investigators. The intervention will be double blind with regard to the coffee type that participants receive (caffeinated and decaffeinated); we will ask the participants about whether they notice the type of coffee they receive.  **Screening** **Initial visit** **4 wk visit 6 wk visit** **8 wk visit**   | Run-in-phase (2 weeks)  (No coffee) | - Caffeinated coffee (n=15) - Decaffeinated coffee (n=15) - No coffee (n=15) | | --- | --- |   **Randomization:**  Randomization will be conducted by a statistician that is not involved in the study using blocking and stratification by sex to avoid differences in the proportion of men and women between the three intervention groups (35).  **Interventions:**  Participants in the intervention groups will consume 5 cups of instant caffeinated or decaffeinated coffee. The instant coffee will be provided in prepackaged plastic cups each containing the same amount of coffee that should be used to prepare one cup of coffee by adding hot water and 5 of these plastic cups are included in 1 bag (supply for 1 day). The 1-cup packages will not provide any clues whether they contain caffeinated or decaffeinated coffee. We will instruct participants on how to prepare the coffee, and ask them to consume a cup with every meal, and at mid-morning and mid-afternoon. Participants will be allowed to adjust the amount of added water according to their preferred coffee strength, but coffee should be consumed without caloric sweeteners. Artificial sweetener will be supplied to participants that prefer sweetened coffee. Participants who are randomized to the control (no coffee) intervention will be instructed to consume 5 cups of water. Before the start of the run-in phase, participants will receive dietary advice from a nutritionist to avoid coffee-related and caffeine-containing foods and drinks other than the coffee that will be provided. They will also be instructed to maintain a stable usual diet (including supplement use and alcohol consumption), and stable physical activity patterns throughout the study. In addition, participants are not allowed to use caffeine-containing medications such as certain flu remedies and analgesics or medications that may interact with caffeine including bronchodilators, quinolone antibiotics, monoamine oxidase inhibitors, anxiolytics, ranitidine, corticosteroids, growth hormone, and antihypertensives. To reduce symptoms related to caffeine withdrawal, we will instruct participants to gradually reduce their coffee consumption at the start of the run-in period and after completion of the trial over three days. We will provide extra coffee to the participants to allow this gradual reduction after completion of the trial.  **Visits**  Visits will be arranged as outpatient visits to the GCRC and none of the visits will not require an overnight stay.  1. Screening visit (1 visit)  The screening visit consists of:   - Signing the informed consent - An interview: medical history, medication use, use of drugs and alcohol, habitual physical activity - A physical examination including measurement of weight and height - An electrocardiogram, a urine HCG pregnancy test (women only), and drawing of fasting blood for blood glucose, liver function tests (AST, ALT, alkaline phosphatase), creatinine, and complete blood count (CBC).   2. Consultation nutritionist and run-in period  Subjects will meet with the nutritionist to receive instructions to avoid coffee-related and caffeine-containing food (other than the coffee provided) during the entire study. They will also be instructed to maintain a stable usual diet, and stable physical activity patterns throughout the study. To document adherence with the diet, subjects will be asked to record the type of foods and the food portions eaten for two weekdays and one weekend day for the week before the post-run-in phase visit and the visits 4 and 8 weeks later. Following this consultation, subjects will enter the 2-week run-in phase, which will serve as a washout period for the effects of previous coffee/caffeine use.  3. Post run-in phase and efficacy assessment visits (three visits)  These visits will occur immediately after the run-in-phase and 4 and 8 weeks after that. During these visits we will:   - Measure weight and waist circumference - Assess body composition using bioelectrical impedance analysis. - Measure systolic and diastolic blood pressure. - Collect fasting blood samples and conduct an oral glucose tolerance test drawing blood at 30 min, 60 min, and 120 min after the oral glucose load. Blood samples will be used to measure glucose, insulin concentrations, and lipid profile (LDL, HDL, and total cholesterol, triglycerides) and will be stored for possible future measurement of intermediary factors (e.g. adipokines). - Supply coffee sachets to the participants and provide instructions on how to prepare the coffee ( post run-in phase visit and week 4 visit only) - Count what is left of the provided coffee sachets to assess compliance (week 4 and week 8 visit only). Subjects will be invited to provide their ideas regarding possibilities to improve compliance. - Collect the 3-day dietary records and diaries in which participants will document deviations from the intervention protocol.   4. Visit with nonfasting blood draw (one visit)  This visits will occur in the afternoon 6 weeks after the run-in-phase. During this visit we will measure weight and systolic and diastolic blood pressure and collect a nonfasting blood sample. This sample will be used to measure s**erum caffeine concentrations to assess compliance.**  **Consistency of the provided coffee**  We will obtain instant coffee that is from the same batch to reduce variation in coffee characteristics. Also, we will store the product under optimal conditions (e.g. closed containers) and we will measure the amount of caffeine in caffeinated and decaffeinated coffee samples obtained at the start (that will be frozen) and at the end of the study.  **Technology employed in the study**  Demographic data and medical history: obtained by using a standardized questionnaire.  Anthropometry: Body weight, height and waist circumference will be measured according to standard protocols. The body mass index (BMI) is calculated as the weight (kg) over height2 (meters squared). Body composition will also be assessed by bioelectrical impedance analysis, using a single frequency bioimpedance analyzer (model 101, RJL Systems, Mt. Clemens, MI), and fat-free mass (FFM) and fat mass (FM) will be calculated (36). This method has previously been validated by comparison with DEXA measured FM (r=0.91) (37).  Dietary data: Using 3-day dietary records (2 weekday and 1 weekend day) we will calculate total energy intake, the number and distribution of meals and snacks, macro-and micronutrient intakes, and consumption of foods and drinks (particularly carbonated beverages and dairy using the Nutritionist Five program (First Data Bank, San Bruno, CA).  Assessment of blood pressure: blood pressure will be measured using multiple repeated measured with automatic Dinamap blood pressure meters using measurements after the participants has been seated for at least 5 minutes.  Oral glucose tolerance test (OGTT): An OGTT will be conducted in the morning starting before 10 am. Subjects will be instructed not to eat or drink after 8 pm not to use coffee after 5 pm on the preceding day. The glucose load will consist of 75 g glucose anhydrate in 300 ml of water ingested over the course of 5 min. An intravenous catheter will be placed in the forearm and blood samples will be collected before the oral glucose load (fasting), after 30 min, 60 min, and 120 min.  Laboratory data: Insulin will be measured using ELISA without cross-reactivity for pro-insulin, glucose will be measured using a photometric method. Fasting triglycerides and lipoprotein profile will be measured in a certified clinical lipid lab using standard methods (38,39). **Serum caffeine concentrations will be measured (using HPLC) in nonfasting blood samples obtained at the 6-week visit and in the coffee samples. B**lood samples will be stored for future determination of other possible intermediary effects of coffee using other funding sources.  Assessment glucose tolerance and insulin resistance: We will use the glucose area under the curve and 2-hr glucose as measures of glucose tolerance. Higher coffee consumption was associated with lower 2-hr glucose concentrations during an oral glucose tolerance test in several cross-sectional studies (5,29). We will calculate the ratio between the 30 min increment in insulin to 30 min increment in glucose concentration as a measure of early insulin secretion (40). We will calculate the homeostasis model assessment of insulin resistance calculated using the following formula: insulin resistance = fasting insulin x glucose / 22.5 (41). In addition, we will calculate the composite insulin sensitivity index (CISI) using the formula {10,000/the square root of [(fasting glucose x fasting insulin) x (mean glucose x mean insulin)]} during the oral glucose tolerance test. This measure has been shown in validation studies to provide a reasonably good measure of insulin resistance (42). |

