### B. Statistical Considerations

| SAS 8.2 (SAS Institute Inc., NC, USA) will be used for statistical analyses. All safety and adverse event data will be summarized separately for each group. The statistical analysis of the data will follow a standard intention to treat analysis. Changes in glucose and insulin concentrations, weight, body mass index (kg/m2), waist circumference, calculated FFM and FM and dietary intake will be evaluated. We will test overall time effects, treatment effects, and time*treatment interactions using ANOVA, and compare the changes in outcome measures between the groups using Student t-tests (if necessary after normalization of the outcome variable, or using the Wilcoxon Rank Sum test). First analyses will be conducted separately for changes between 0 and 4 weeks and for changes between 0 and 8 weeks. If similar results are obtained, the change between 0 weeks and the average of 4 and 8 weeks can be tested to reduce random within person variation. We will also conduct a data analysis stratifying by habitual coffee consumption before the start of the trial (i.e. 1-2 cups, 2-4 cups and >4 cups per day).  A goal of this pilot study is to obtain information on differences in outcome measures and variation to be used in a power analysis for a ‘definite’ trial which will be proposed in a future R01. The available data is insufficient to conduct a power analysis for effects of coffee on the outcome measures at this point, but previous dietary intervention studies of smaller size and shorter duration have been able to detect effects on parameters of glucose metabolism (43). |
| --- |

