#### B5. POSSIBLE RISKS AND ANALYSIS OF RISK/BENEFIT RATIO

| Risks to the subjects will be minimal, including slight pain, or bruise at the site of venipuncture. Potential side effects of the coffee use and caffeine withdrawal will be monitored closely. Caffeine abstinence can lead to withdrawal symptoms in regular caffeine users including headaches, fatigue, decreased energy/ activeness, decreased alertness, drowsiness, decreased contentedness, depressed mood, difficulty concentrating, irritability, being foggy/not clearheaded, flu-like symptoms, nausea/vomiting, and muscle pain/stiffness (44). Typically, symptoms of caffeine withdrawal have a peak intensity after 1-2 days and have a duration of 2-9 days (44). Increases in homocysteine concentrations (45) and blood pressure (average increase: 1.2 mmHg for systolic and 0.5 mmHg for diastolic blood pressure) (46) have been reported as a results of (caffeinated) coffee consumption and systolic and diastolic blood pressure will be measured at each visit. If any serious side effects of the interventions are detected, participants will be withdrawn from the study protocol.  Risk protection / prevention procedures  We will ask the subjects to stay in close communication with us in case any symptoms that could possibly be attributed to the study. One of the investigators will carry a pager at all times for 24 hour per day access by subjects. Confidentiality will be maintained through our computer‑based data coding system. Results obtained from individual subjects will be analyzed, reported and discussed in reference to the subjects code. The principal investigator will maintain complete control over all data. If there appears to be good reason to share information with other investigators this will be done only by reference to the subject's entry code. |
| --- |

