#### B6. RECRUITMENT AND CONSENT PROCEDURES

| Recruitment Strategy  We plan to enroll ~45 subjects over 4 weeks. To achieve this, we will need to screen approximately 20-25 subjects per week at the GCRC (to have 1 subject meeting the study eligibility criteria out of approximately 2 subjects screened). We expect that the number of persons that has to visit the hospital for screening will be relatively low because the eligibility criteria are not very restrictive and can to a large extent be assessed through a preceding telephone interview. We will recruit from the Boston community through advertisements and posters. We have extensive experience with recruiting and screening subjects and have previously used successfully the techniques we propose to use herein. Thus, we do not feel that enrolling the number of patients needed would pose any problems.  Consent procedures  The purpose of the study, the risks involved, reimbursements for study related costs, and the importance of the subject's full cooperation will be explained to each subject and will also be included in the consent document, which each subject will read and sign before entering the study. Details of the protocol will be explained to subjects and written informed consent will be obtained. The subjects also will be informed that they may withdraw from the study at any time. Constant medical supervision will be provided throughout the study period. A copy of the protocol and the consent form will be given to each patient and a copy of the consent form will be archived. |
| --- |

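### No scheduled visit asks about symptoms, so the adverse event summary by group rests on participant-initiated reports that can differ between the coffee and water arms

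*Protocol*

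**What the plan says.** Section B5 commits to surveillance: "Potential side effects of the coffee use and caffeine withdrawal will be monitored closely". It lists more than a dozen withdrawal symptoms, starting with headache and fatigue. For learning of symptoms it gives this route: "We will ask the subjects to stay in close communication with us in case any symptoms that could possibly be attributed to the study". The contact channel is a pager: "One of the investigators will carry a pager at all times for 24 hour per day access by subjects".

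Two other safety elements are stated. B5 says that "systolic and diastolic blood pressure will be measured at each visit", and B6 says "Constant medical supervision will be provided throughout the study period", with no procedure attached.

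The Statistical Considerations promise an output: "All safety and adverse event data will be summarized separately for each group".

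The Study Design section itemizes each visit. Participants keep dietary records and "diaries in which participants will document deviations from the intervention protocol". Blinding of participants is limited to whether the coffee is caffeinated or decaffeinated.

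**The concern.** A comparison of adverse events between arms is only as good as the equality of ascertainment. Here symptoms reach the data when a participant chooses to raise them and sees a possible link to the study. That link can look different to someone who knows they drink water and someone who knows they drink coffee. The summary by group could then show a difference in reporting rather than in symptoms, or hide a real one.

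The rule in B5 for withdrawing participants also takes effect only when a serious side effect is detected, so it too depends on ascertainment. An analysis plan written later cannot repair this, because it cannot recover symptoms that nobody asked about. The place to settle it is the protocol's visit schedule.

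**Working it through.** The protocol states no figure for this point. The check is a reading of the procedure lists, followed by two short calculations.

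**1. What each visit collects (Study Design, Visits)**
- Post-run-in, week 4 and week 8: weight, waist, impedance, blood pressure, fasting blood and glucose tolerance test, dietary records and diaries. Coffee is supplied at the first two. Leftover sachets are counted at weeks 4 and 8, and participants are invited to suggest ways to improve compliance.
- Week 6: weight, blood pressure, nonfasting blood sample.
- Symptom question, adverse event question or withdrawal scale: none at any of the four.

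The lists are detailed enough to include asking for ideas on compliance, so brevity does not readily explain the omission.

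**2. What remains for symptoms**

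The diaries are assigned to protocol deviations. That leaves the B5 request to stay in touch, with the pager as one channel. Both depend on the participant.

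**3. Effect of unequal reporting**

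Let p be the true proportion with a symptom, the same in both arms, and let r_c and r_w be the probabilities that an affected participant reports it in a coffee arm and in the water arm.

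Apparent ratio = (p × r_c) / (p × r_w) = r_c / r_w

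The documents give neither p nor the reporting probabilities. For illustration, assume 6 of 15 affected in each arm (15 per arm is the protocol's figure):

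| r_c | r_w | expected reports, coffee v water | apparent ratio |
| --- | --- | --- | --- |
| 0.8 | 0.8 | 4.8 v 4.8 | 1.0 |
| 0.8 | 0.5 | 4.8 v 3.0 | 1.6 |
| 0.8 | 0.4 | 4.8 v 2.4 | 2.0 |
| 0.4 | 0.8 | 2.4 v 4.8 | 0.5 |

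The table shows the mechanism and that it can run either way. It does not estimate the bias in this trial.

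**4. When withdrawal symptoms would fall**

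Inputs: taper of 3 days at the start of the run-in and again after the trial (Study Design); symptoms lasting 2 to 9 days (B5); run-in of 2 weeks, or 14 days.

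- Start of study: 3 + 9 = 12 days at most, inside the 14-day run-in. These symptoms should mostly end before the assigned drink starts, and so differ little by arm.
- End of study: the same 3 + 9 = 12 days would follow week 8. No visit is planned then, and withdrawal would be expected mainly in the caffeinated arm.

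The period in which withdrawal should differ most by arm is thus covered by participant-initiated contact alone.

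**5. Gap at the start of the intervention**

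After the post-run-in visit the next scheduled visit is week 4, which is 28 of the 56 intervention days.

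**The case against.** **Safety is not wholly passive.** Blood pressure, the coffee effect for which B5 gives an average size, is measured at the visits in all arms. Staff see participants in person at the end of the run-in and at weeks 4, 6 and 8, and B6 states constant medical supervision. This stands. A reader might infer that side effects are known only if a participant telephones, or that monitoring is absent. The documents support neither; they support only that no procedure for asking about symptoms is described.

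**The reporting threshold is low.** B5 refers to any symptom with a possible link to the study and does not say who judges the link. This weakens the filter but does not remove it, because the participant must still speak first.

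**The direction of bias is not fixed.** A reader might infer that water drinkers will under-report. They knowingly abstain from caffeine, however, and headache heads the B5 list of abstinence symptoms, so they could report more. This stands: bias is possible, and neither its sign nor its certainty is established. Between the two coffee arms, blinding limits the problem unless participants recognise their coffee.

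**Early side effects.** A reader might use the background remark that "effects of caffeine on epinephrine levels wane after continued intake" to argue that side effects peak before week 4. That remark concerns whether acute effects on insulin sensitivity carry over to long-term coffee use. It is not about symptoms and does not support the argument.

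**Small, minimal-risk pilot.** The promised safety summary is descriptive, and with 15 per arm it could not settle much: 4 v 2 of 15 gives a two-sided Fisher p of about 0.65. Tolerability is not among the stated aims, which are adherence, body weight, postload glucose and markers of insulin sensitivity. This limits the weight of the point. It does not justify unequal ascertainment when the remedy is cheap.

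**Conclusion.** The point holds in limited form. For symptoms, the protocol describes only participant-initiated reporting of what could be linked to the study, while promising close monitoring and a summary by group. Followed as written, the coffee and water arms can be ascertained unequally, in either direction. The size cannot be derived from the documents: with equal true rates the apparent ratio is r_c / r_w, which is 1.0 if reporting is equal and runs from 0.5 to 2.0 over assumed reporting probabilities of 0.4 to 0.8.

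The conclusion rests on two readings: that the itemized visit lists are complete, and that participants given water know their assignment. It does not extend to blood pressure, which is measured alike in all arms. It applies only weakly to caffeinated against decaffeinated coffee, and it does not show that the summary will be biased. It is a modest design correction that should be made before enrolment.

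**What to change.** 1. Add one fixed symptom checklist, identical in all three arms and asked whether or not the participant links the symptom to the study, to the post-run-in visit (covering the run-in) and to the week 4, 6 and 8 visits. Use the withdrawal symptoms already listed in B5 plus the coffee side effects the investigators expect.
2. Put the same tick-list in the existing diary for the first week of the intervention and for the post-trial taper. On the protocol's own figures the latter page should span about 12 days (3 + 9). No visit follows week 8, so it needs a return route such as mail or a short call.
3. State in the Statistical Considerations that the summary by group is based on these solicited data, with spontaneous reports listed separately.

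Cost: one form, a diary page, a few minutes at visits that already take place, and one return of the last page. Symptom counts will be higher than under spontaneous reporting, which should be said when they are presented.
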